### Sample size calculation

2.9

The sample size is calculated by using the software PASS 2011. Based on the analysis of the variance of means, and estimating an alpha risk of 5% (0.05), a beta risk of 10% (0.10), a unilateral contrast, a typical deviation of 10% (0.10). The primary outcome is the HHS, according to Wang j et al,^[25]^ 6 months after HA, the mean value of Harris score was 86.580 and the standard deviation was 4.629. The experimental assumed the mean value of the monitoring group is 92.650 and the standard deviation is 3.664, and a rate of follow-up losses of 20%, 11 subjects are required in each group, combined with the actual situation of patients in the hospital. Finally, we will include 50 patients divided into 2 groups, each group contains 25 subjects, to overcome this value to assume the possible loss of follow-up, the calculation results are shown in Figure 6.

**Figure 6 F6:**

Sample size calculated by PASS 2011.

### Data management and statistical analysis

2.10

Data are collected from electronic medical records at the study sites, participants study-specific diaries. All collected data for the trial is entered electronically in the encrypted database built by the researchers ourselves which could not be accessed by a third party. The system sets a fixed personal account according to the users organization and role. All attempts to log in to the system will be recorded. All data changes are recorded by user and time, so it can be tracked. All the research data were collected in the First Affiliated Hospital of Guangzhou University of Traditional Chinese Medicine, part of which was recorded in the orthopedic ward and some in the outpatient department. The data management system will check whether all the input data are of correct type, for example, the date must be valid date, and the number must be valid number, at the same time, logical check/verification is designed. Composition of data monitoring committee (DMC) will be undertaken by the Ethics Committee of the First Affiliated Hospital of Guangzhou University of Traditional Chinese Medicine and responsible for reviewing data security once a year.

The statistical analysis will be carried out by IBMSPSS Statistics 21 software. Demographic and baseline data will be summarised using descriptive statistics and graphs as appropriate. Continuous variables will be summarised by descriptive statistics. Categorical variables will be summarised in frequency tables. For the contrast of intragroup hypotheses, Student *t-*test for paired variables will be applied in the case of parametric distribution and Kruskal–Wallis H for nonparametric distributions. Kolmogorov Smirnov test will be used to test the normality of variables. One-factor analysis of variance (ANOVA) will be used in the case of parametric distributions and Kruskal–Wallis H for non-parametric distributions. Statistical tests used to compare between treatments groups will be done two-sided at a signifi-cance level of 5%. The confidence level used will be 95% (0.05), and the power of the study will be 90% (0.1).

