These variables will be measured in the pre-evaluation, first evaluation (week 2), second evaluation (week 4, short-term), third evaluation (week 12, medium-term), and fourth evaluation (week 24, the end of the study). These evaluations will be carried out by an evaluator trained in these procedures, and the data will be stored in an Excel document.

Baseline information of diagnosis and treatment, such as gender, age, comorbidities, imaging, previous self-care ability, injury mode, fracture classification, and potential previous treatment, such as other site fractures, soft tissue injuries, osteoporosis, etc, will be collected from participants medical records.

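### The within-group sentence names Kruskal–Wallis H, an independent-samples test, as the non-normal counterpart of the paired t-test; it should name a paired rank test

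*Protocol article*

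**What the plan says.** Section 2.10 (Data management and statistical analysis) of the protocol article sets out two families of tests.

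- **Within group.** The sentence opens "For the contrast of intragroup hypotheses" and says that Student's t-test for paired data "will be applied in the case of parametric distribution and Kruskal–Wallis H for nonparametric distributions".
- **A separate, later sentence** names one-factor ANOVA, which "will be used in the case of parametric distributions and Kruskal–Wallis H for non-parametric distributions". It does not say which comparison it serves, but it fits the comparison of the two arms.

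The branch is chosen by a normality test: "Kolmogorov Smirnov test will be used to test the normality of variables".

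Section 2.7.2 shows that the within-group data are repeated measurements on the same people: "These variables will be measured in the pre-evaluation, first evaluation (week 2), second evaluation (week 4, short-term), third evaluation (week 12, medium-term"), followed by a fourth evaluation at week 24. Section 2.9 gives the size: "we will include 50 patients divided into 2 groups, each group contains 25 subjects", with an allowance of 20% for loss to follow-up.

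No signed-rank or Friedman test is named anywhere in the article.

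**The concern.** Kruskal–Wallis H pools all observations, ranks them, and judges the difference in mean ranks against the variation expected if the samples came from different, unrelated people. Two visits of one patient are not unrelated. When a patient's scores are positively correlated across visits, part of the between-patient variation cancels in the before–after difference. A paired test uses that cancellation; Kruskal–Wallis does not. Its reference variance is then too large and its P values are too large.

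What is at stake is the description of recovery within each arm. An outcome classed as non-normal would be tested with a method much weaker than the one used for an outcome classed as normal, and a modest real change between visits could be reported as no change. Timed up-and-go (a time in seconds) and pain on the VAS (bounded at 0) are plausible candidates for that branch, although the article does not say how they are distributed.

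**Working it through.** **Figures in the plan.** The article gives no figure for the within-group analyses, so there is none to reproduce here. Its sample size rests on the between-arm difference in Harris Hip Score (92.650 − 86.580 = 6.07) and uses no paired test. The choice of within-group test therefore does not enter it.

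**Inputs**
- Pairs per group: 25 × (1 − 0.20) = 20 (section 2.9).
- Nominal level: 5%, two-sided. Section 2.10 states this for the between-group tests; it is carried over here.
- Correlation between two visits of one patient: not in the documents. Assumed 0.3, 0.5 and 0.7.
- Size of the within-group change: not in the documents. Assumed 0.5 SD and 1 SD.

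**Step 1: approximate type I error by hand.** With two visits and no true change, correlation shrinks the variance of the difference in mean ranks by the factor (1 − ρs), where ρs is the rank correlation. Kruskal–Wallis does not know this, so it rejects only when a standard normal variable exceeds 1.96/√(1 − ρs). For an underlying normal correlation ρ, ρs = (6/π)·arcsin(ρ/2).

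| ρ | ρs | 1.96/√(1 − ρs) | Two-sided rejection rate |
|---|---|---|---|
| 0.3 | 0.288 | 1.96/0.844 = 2.32 | 2.0% |
| 0.5 | 0.483 | 1.96/0.719 = 2.72 | 0.6% |
| 0.7 | 0.683 | 1.96/0.563 = 3.48 | 0.05% |

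**Step 2: simulation at n = 20 pairs.** The data are right-skewed (lognormal) pairs. Results of two independent runs are separated by a slash.

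| ρ | Type I error, Kruskal–Wallis | Power at 0.5 SD, Kruskal–Wallis | Power at 0.5 SD, signed-rank |
|---|---|---|---|
| 0.3 | 1.9% / 2.4% | 28% / 29% | 37% / 38% |
| 0.5 | 1.2% / 0.9% | 27% / 28% | 52% / 49% |
| 0.7 | 0.2% / 0.1% | 23% / 23% | 73% / 70% |

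In the second run the signed-rank test stayed between 4.6% and 5.5% under no change for every correlation from 0 to 0.9. Kruskal–Wallis held its level only at correlation 0 (5.1%).

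**Step 3: larger changes.** At 1 SD the power of Kruskal–Wallis against signed-rank is 87% vs 92% (ρ = 0.3), 92% vs 98% (0.5) and 96% vs 100% (0.7). From 1.5 SD both are near 100%.

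**Step 4: all five time points together.** With n = 20 and ρ = 0.5, type I error is 0.2% for Kruskal–Wallis and 4.7% for Friedman. Power for a 0.5 SD shift at one visit is 13% against 47%.

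**The case against.** **It may be a slip of wording, with the between-group test meant.** The text does not allow that reading. The sentence is explicitly about within-group hypotheses and gives the paired t-test as the normal-theory partner, and the later sentence already pairs Kruskal–Wallis with ANOVA. Nor is this a detail left to an analysis plan that is not shown: a specific test is named, and it is the wrong one for paired data.

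**The trial's question is the randomised comparison.** This stands. Kruskal–Wallis is valid for two independent arms. Both arms follow the same basic rehabilitation programme and are expected to improve, so change within one arm cannot show that the monitoring system works.

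**The loss depends on assumed values.** This also stands. Recovery from soon after surgery to week 24 may be large, and then either test would detect it. The loss matters for small changes, for instance between neighbouring later visits.

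**Stronger readings that the documents do not support.** A reader might infer that false claims of improvement will follow. With positive correlation the opposite holds: P values are too large. A reader might also infer that the Kolmogorov–Smirnov switch is itself an error and must be replaced by tests or models fixed per outcome. Pre-testing for normality is common and contradicts nothing in the article, so that is a preference. For a distribution with skewness 1 and 20 to 25 patients, the pre-test rejects in about 21% of samples with the Lilliefors correction and under 1% without it; the article does not say which version is meant. On those figures a moderately skewed outcome would usually go to the paired t-test, so it cannot be claimed that skewed outcomes will as a rule reach the wrong test.

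**Conclusion.** The sentence is wrong as written, and nothing else in the article corrects it: an independent-samples test is prescribed for repeated measurements on the same patients. If visits correlate at 0.3 to 0.7 and 20 pairs per group remain, the actual type I error is about 2% down to 0.2% instead of 5%. For a change of 0.5 SD, power is about 23% to 28% where the signed-rank test would have 37% to 73%. Correlation and effect size are both assumptions. With uncorrelated visits there would be no error in level, and at 1 SD or more little power is lost.

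The reach is limited to within-group analyses that fall into the non-normal branch. The paired t-test branch, the between-group comparison of the Harris Hip Score and the sample size are unaffected. It should be fixed, as an error in a supporting analysis; it does not threaten the trial's main conclusion.

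**What to change.** In the within-group sentence of section 2.10, replace Kruskal–Wallis H by the Wilcoxon signed-rank test where two visits are compared, or by the Friedman test where several visits are compared together. State that Kruskal–Wallis H is kept for the between-group comparison only, which also makes clear what the ANOVA sentence refers to.

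The cost is one edited sentence. Both tests are standard procedures. No new data, visit or change in sample size is needed.

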#### The primary outcome

2.7.1

The primary outcome is a change in the Harris Hip Score (HHS). HHS is used most commonly as a postoperative functional evaluation tool for hip fractures. The following 7 symptoms can be evaluated by HHS: the degree of the pain, the daily activity function, gait, walking aids, walking distance, deformity degree, and activity scope. The score is judged and recorded by researchers with a totally 100 (excellent: 90∼100, fine: 80∼89, secondary: 70∼79, and not satisfactory: <70), the higher scores indicating better joint function.

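### The named one-factor ANOVA cannot use the earlier HHS values of the 20% of patients expected to be lost; if loss differs by arm, the estimate could shift by about 0.4 to 1.5 points

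*Protocol article*

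**What the plan says.** The protocol article, section 2.7.1, makes a change in HHS the primary outcome and names no visit. The only pointer to a time is section 2.9, whose control figures are for 6 months after surgery.

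The closing text of section 2.7.2 schedules the outcome variables at a pre-evaluation and at weeks 2, 4, 12 and 24. Table 1 does not list HHS, so the earlier values rest on that text.

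For the comparison between groups, section 2.10 names: "One-factor analysis of variance (ANOVA) will be used in the case of parametric distributions and Kruskal–Wallis H for non-parametric distributions". It sets a two-sided 5% level.

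On attrition, section 2.9 assumes "a rate of follow-up losses of 20%, 11 subjects are required in each group" and then enrols 25 per group. Section 2.7.2 counts 6-month mortality as an outcome, so deaths are also foreseen.

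Three statements bear on who is lost. Section 2.6.2 gives the monitoring group daily reminders and online access to the physician. Section 2.6.1 leaves controls to call with questions and rules out proactive calls to them. Section 2.11 lists serious illness, poor compliance and use of another exercise plan among the grounds for leaving the study.

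**The concern.** A one-factor ANOVA or Kruskal-Wallis test takes one value per patient. A patient who leaves after week 12 has HHS values that say a good deal about the likely week-24 score, but the named test has no place for them. That patient either drops out of the comparison or enters with a value supplied by some other rule.

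This matters because loss here may be related both to recovery and to arm. The trial is open, contact between visits differs by group, and some grounds for leaving are linked to how well a patient is doing. If poor recoverers leave mainly from the control group, the remaining controls look better than they should and the device is undersold. If they leave mainly from the monitoring group, the device is flattered. Enrolling more patients corrects neither.

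**Working it through.** **Inputs from the article (section 2.9).** Controls: "the mean value of Harris score was 86.580 and the standard deviation was 4.629". Monitoring group, assumed: "the mean value of the monitoring group is 92.650 and the standard deviation is 3.664". Planned difference 92.650 − 86.580 = 6.07. Loss 20%; 25 per group.

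**Inputs not in the article, assumed.** The HHS gap between lost and retained patients; the correlation between week-12 and week-24 HHS (0.5 to 0.8); how strongly loss depends on week-12 HHS (log-odds 1.5 to 3 per SD). The SD of the *change* in HHS is not given either, so the 6-month SDs are used.

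**Step 1: the plan's own figure.** Common SD = √((4.629² + 3.664²)/2) = 4.174. A one-sided 5% test with 90% power needs 9 per group. With 20% loss this becomes 9 × 1.2 = 10.8, so 11, or 9/0.8 = 11.25, so 12. The stated 11 is reproduced.

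**Step 2: power is not the problem.** 25 × 0.8 = 20 per group remain. Two-sided power for 6.07 points is then 99.4%. The standard error of the difference is √((4.629² + 3.664²)/20) = 1.32.

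**Step 3: bias by hand.** If a share q of an arm is lost and the lost patients score k SD below the retained, the mean of the retained is too high by q × k × SD. With q = 0.2 and k = 1:
- controls only: 0.2 × 4.629 = 0.93
- monitoring only: 0.2 × 3.664 = 0.73
- both arms, same direction: 0.2 × (4.629 − 3.664) = 0.19
- both arms, opposite directions: 0.2 × (4.629 + 3.664) = 1.66
- loss unrelated to HHS: 0

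**Step 4: simulation.** 25 per arm, normal week-12 and week-24 HHS, 20% lost per arm, loss logistic in week-12 HHS, no true difference, observed week-24 values compared two-sided at 5%. In the one-arm and same-rule rows it is the low scorers who are lost.

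| HHS-related loss | Bias (points) | Rejection | Favours |
|---|---|---|---|
| None (random loss) | about 0 | about 5% | neither |
| Same rule in both arms | 0.1–0.2 | about 5% | control, slightly |
| Controls only | 0.5–1.1 | 6–14% | control |
| Monitoring only | 0.4–0.85 | 6–10% | device |
| Opposite directions, log-odds 1.5 | about 0.9–1.5 | 11–22% | the arm losing its poor recoverers |

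The one-arm biases add when the directions are opposite, so at log-odds 3 and correlation 0.8 the total would be near 1.12 + 0.85 = 1.97. The ranges follow from the assumptions and are not limits.

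**Step 5: using the earlier score.** A regression estimate that brings in week-12 HHS, standing in for a repeated-measures model, has bias below 0.05 points in these settings. This is expected, because loss was made to depend on that score alone and every patient had one. If half the lost patients have no earlier value, about 0.28–0.50 points remain (correlation 0.7 with log-odds 1.5; correlation 0.8 with log-odds 3).

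**Step 6: against the planned effect.** 0.4/6.07 = 7% and 1.1/6.07 = 18% for one-arm loss; 1.5/6.07 = 25% for opposite loss. With a true 6.07-point difference, the strongest controls-only setting (correlation 0.8, log-odds 3) still leaves power of about 97%.

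**The case against.** The strongest reply is that the article names a test, not an analysis population or a missing-data rule. Such rules commonly sit in a full protocol or analysis plan that is not shown, and an ANOVA can be run on imputed values. That stands. A reader might infer that the plan analyses completers only, but the article does not say so and the absence of a rule is not the point here. What survives is narrower: the chosen test cannot itself use HHS values that the plan collects.

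Two further readings go too far. One is that the bias is capped at about 1 point. The documents give no basis for any cap; that size fits one pattern, a gap of about 1 SD in the control arm alone. The other is that the false-positive rate exceeds 5% whatever the pattern. It does so only if HHS-related loss differs by arm. With controls-only loss, the excess rejections favour control, and false claims for the device fall to about 1% or less against a nominal 2.5%.

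It is also fair to say that the mechanisms are assumed, that log-odds of 1.5 to 3 per SD is strong dependence (odds ratios of about 4.5 to 20), and that raw-score SDs stand in for the unknown SD of change. The sizes are therefore illustrative. The plan's 20% is a sample-size allowance and observed loss may be smaller.

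**Conclusion.** The point holds as an improvement to the named method, not as an error that undermines the trial. The plan collects HHS at several visits, expects one patient in five to be lost, and names a test that uses one visit. The bias depends on the pattern of loss: about 0 if random, 0.1–0.2 points if alike in both arms, 0.4–1.1 points if HHS-related in one arm only, and up to about 1.5 points for moderate dependence in opposite directions. It favours the device when poor recoverers leave mainly from the monitoring arm.

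These sizes assume 20% loss per arm, the 6-month SDs, a week-24 analysis and a correlation of 0.5–0.8. Bias in points scales with the SD, so a different SD of change would scale it in proportion. A bias of this size would not hide a true 6.07-point effect. It would misstate the size of the effect and would matter more if the true effect is smaller.

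**What to change.** Make the primary between-group analysis a linear mixed model for repeated measures on HHS at weeks 2, 4, 12 and 24, with group, visit, group-by-visit and an unstructured covariance, in all randomised patients with any HHS value. Name the week-24 group contrast as primary.

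Include the pre-evaluation HHS, as a covariate or as the first element of the outcome vector. The second form is preferable, because only then does a patient lost before week 2 contribute; protection for such patients remains partial.

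Keep the rank test as a sensitivity analysis, with deaths ranked below the lowest observed HHS, and report deaths by arm. The rank test also covers the ceiling at 100, since the mixed model is normal-based and projects a week-24 score for patients who died.

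Cost: changed wording and a little more analysis work in the SPSS software already named, with no new visits or data. The model relies on loss depending only on recorded values, which is weaker than what an analysis of observed week-24 values needs. An unstructured covariance has 4 × 5/2 = 10 parameters for four visits, or 5 × 6/2 = 15 with the pre-evaluation in the outcome vector. With 50 patients, a simpler fallback structure should be named in advance.

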### Study design and setting

2.1

This is an opening, prospective, double-dummy RCT. There are 50 patients in total with femoral neck fracture will be recruited from the First Affiliated Hospital of Guangzhou University of TCM, Guangzhou, China. The flow chart and study period are shown respectively in Figure 1. After obtaining written informed consent, the eligible participants will get complete examination before surgery as well as hemiarthroplasty, and then they will be randomly assigned to a monitoring group or a control group in a 1:1 ratio.

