### Participants

2.2

Participants will be recruited via inpatients of a standard-compliant femoral neck fracture, which had a clear history of trauma, hip or greater trochanteric pain, aggravating during activity and was forced to bend the hip and knee, the deformity of pronation and adduction was common. Participants should meet the X-Ray and CT images of a femoral neck fracture. The information about the study, the use of the monitor, and the schedule will be carefully explained before enrollment.

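### The primary outcome is a change in HHS, but the sample size rests on the 6-month HHS level and the named between-group test has no baseline covariate

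*Protocol article*

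**What the plan says.** - **Endpoint.** Section 2.7.1: "The primary outcome is a change in the Harris Hip Score (HHS"). It names neither the reference visit nor the target visit.
- **Visits.** The closing text of section 2.7.2: "These variables will be measured in the pre-evaluation, first evaluation (week 2"), followed by weeks 4, 12 and 24. The pre-evaluation has no date. Section 2.1 says "the eligible participants will get complete examination before surgery as well as hemiarthroplasty", with randomisation afterwards; HHS is not mentioned there. Table 1 schedules assessments only from week 2, and none of its rows is HHS.
- **Sizing.** Section 2.9 calls the primary outcome simply the HHS. It takes a 6-month mean of 86.580 (SD 4.629) from a cited study and assumes 92.650 (SD 3.664) under monitoring. It allows 20% loss, arrives at 11 per group and recruits 25 per group. No SD of change and no correlation enters.
- **Analysis.** Section 2.10: "One-factor analysis of variance (ANOVA) will be used in the case of parametric distributions", with Kruskal–Wallis otherwise. It does not say to which variable or visit the test applies. It repeats the 90% power.

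**The concern.** A power statement holds only for the quantity whose SD went into it. Here that quantity is a 6-month score, while the declared endpoint is a difference between two scores. The SD of a difference depends on the baseline SD and on the correlation between the two measurements, and the plan states neither.

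If the pre-evaluation precedes surgery, it scores patients with an acute fracture; section 2.2 describes "hip or greater trochanteric pain, aggravating during activity and was forced to bend the hip and knee". HHS rates pain, gait, walking aids and walking distance, so such a score may say little about function 24 weeks after a prosthesis. Subtracting a weakly related baseline adds variance instead of removing it. A one-factor ANOVA cannot put this right, because it holds no term for the baseline.

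At stake are the precision of the main result and a clear answer to which number is the primary result.

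**Working it through.** **Inputs from section 2.9.** Difference 92.650 − 86.580 = 6.07. Pooled SD = √((4.629² + 3.664²)/2) = 4.174. Standardised difference 6.07/4.174 = 1.454. Loss 20%, so 25 recruited leaves 25 × 0.8 = 20 completers per group.

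**Step 1: the plan's own figure.** Section 2.9 sets out "estimating an alpha risk of 5% (0.05"), 90% power and "a unilateral contrast". On the 6-month level, a one-sided test needs 9 per group; 9 × 1.2 = 10.8 gives 11, and 9/0.8 = 11.25 gives 12. A two-sided t-test needs 11 before loss (power 0.900). Either way the stated 11 is recovered from the 6-month level. (Sizing is one-sided and testing in section 2.10 is two-sided; that is a separate matter. Two-sided 5% is used below.)

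**Step 2: the three candidate analyses.** Let k be the baseline SD divided by the week-24 SD, and rho the baseline-to-week-24 correlation.
- Week-24 score, unadjusted: SD = 4.174.
- Change: SD = 4.174 × √(1 + k² − 2·rho·k).
- ANCOVA on week 24: residual SD = 4.174 × √(1 − rho²), with one fewer degree of freedom.

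Change is noisier than the week-24 score only if k² − 2·rho·k > 0, that is rho < k/2. In units of the week-24 variance, change exceeds ANCOVA by (1 + k² − 2·rho·k) − (1 − rho²) = (k − rho)², which is never negative. The unadjusted score exceeds ANCOVA by rho², also never negative.

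**Step 3: numbers.** k and rho are assumptions. Power is from the noncentral t with 20 completers per group; n is per group for 90% power before loss.

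| k | rho | SD of change | n, change | Power, change | n, ANCOVA | Power, ANCOVA |
|---|---|---|---|---|---|---|
| 1 | 0 | 5.90 | 21 | 0.887 | 12 | 0.994 |
| 1 | 0.1 | 5.60 | 19 | 0.916 | 11 | 0.994 |
| 1 | 0.3 | 4.94 | 15 | 0.966 | 11 | 0.997 |
| 1 | 0.5 | 4.17 | 11 | 0.994 | 9 | 0.999 |
| 1 | 0.7 | 3.23 | 8 | >0.999 | 7 | >0.999 |
| 1.5 | 0 | 7.53 | 34 | 0.700 | 12 | 0.994 |
| 1.5 | 0.3 | 6.40 | 25 | 0.832 | 11 | 0.997 |
| 1.5 | 0.5 | 5.52 | 19 | 0.923 | 9 | 0.999 |

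The unadjusted week-24 score needs 11 per group and has power 0.994 with 20.

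**Step 4: the price of ANCOVA.** In the worst case, rho = 0, losing the degree of freedom leaves power at 0.994 with 20 per group and takes it from 0.900 to 0.899 with 11. These figures treat the baseline as balanced between arms; chance imbalance costs slightly more.

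**The case against.** **The analysis may already be the sized one.** Section 2.10 attaches no variable to the ANOVA, and section 2.9 speaks of the HHS and of a variance analysis of means. A between-group ANOVA of the week-24 score is a fair reading, and on it no noise is added. This stands: a reader might infer that the plan tests change from a pre-surgery score, but that comes from combining sections 2.7.1 and 2.10. The mismatch in section 2.7.1 remains either way.

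**Before surgery is also an inference.** Sections 2.1 and Table 1 suggest it; nothing states it for HHS. This stands too, and is why the visit needs a date.

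**The noise is not certain.** With equal SDs, change and week-24 score tie at rho = 0.5, and change does better at 0.7. Correct. A low correlation is plausible after an acute fracture but is not documented.

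**The trial is not short of patients in the plain scenario.** With equal SDs and rho 0.1 to 0.3, change keeps power 0.92 to 0.97, above the planned 90%. A reader might infer a badly underpowered trial by supposing a baseline SD twice the week-24 SD (power 0.55 to 0.63 for the same rho), but no passage supports that doubling.

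**ANCOVA adds little to an unadjusted week-24 test.** At rho 0.1 to 0.3, power is 0.994 to 0.997 against 0.994. True: most of the gain comes from naming week 24. An unadjusted comparison is also valid under randomisation. ANCOVA is still preferable, because apart from the degree of freedom it matches or beats both alternatives whatever k and rho turn out to be.

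**Conclusion.** The point holds as a mismatch between three stated elements: a change endpoint without visits, a sample size built on the 6-month level, and a between-group test without the baseline. The 11 per group and 90% power do not carry over to a change in HHS.

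Its size depends on two unknowns. With 20 completers per group, the 6.07-point difference and pooled SD 4.174, power on change runs from 0.89 (rho 0) to 0.994 (rho 0.5) with equal SDs, and is 0.70 to 0.83 (rho 0 to 0.3) at k = 1.5; that k is itself only an illustration. The document does not support saying that the trial is underpowered. It supports saying that its power for the stated endpoint is unknown, and that a near-costless change of wording removes the dependence on those unknowns. This should be changed before analysis; it does not undermine the design.

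**What to change.** 1. In section 2.7.1, name HHS at week 24 as the primary endpoint, which matches section 2.9.
2. In section 2.10, state its analysis: ANCOVA with group and pre-evaluation HHS, reporting the adjusted difference with its 95% CI. If the sponsor prefers to present change, ANCOVA of change with the same baseline covariate gives the same group difference.
3. State when the pre-evaluation takes place relative to surgery and randomisation.

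Age and previous self-care ability are already collected and could be added as covariates; this is optional.

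Minor: the sentence beginning "These variables will be measured in the pre-evaluation" follows a list that includes postoperative complications, 6-month mortality and the timed up-and-go. The first two cannot exist before surgery. The third requires standing and walking, so its entry must be reconciled with the patients' condition at that visit.

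Cost: wording and one degree of freedom for the baseline covariate. No new patients or visits are needed, and pre-evaluation HHS is already among the planned measurements.
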